#### Sub-group analyses

Two groups of participants will be defined regarding their level of knowledge (sufficient / insufficient). Fisher’s exact tests will be used to assess if knowledge is associated with the level of numeracy (yes/no) and with achievement of goals (yes/no). T-test for paired samples will be used to assess differences in knowledge between T1 and T2 in the intervention group. Analyses of variance (ANOVA) will be used to assess if knowledge is associated with age (groups 40–49; 50–59; 60–69). Spearman’s Rho correlation coefficient will be used to assess if knowledge is associated with social status.

Mann Whitney U-tests will be calculated to assess if heart attack risk and social status are associated with the achievement of goals (yes/no).

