## Objectives

Primary objective is to investigate if the ISDM programme is superior to the control-intervention regarding patients’ knowledge and realistic expectations concerning benefits and harms of the available treatment options. Key secondary objective is to determine if patients in the ISDM group achieve their individual treatment goals better than patients in the control-group. Additional objectives are to assess if patients presenting high numeracy levels achieve better knowledge than patients presenting low numeracy, if social status correlates to the level of knowledge, and if patients with good knowledge achieve their treatment goals better than patients with poor knowledge.

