#### Secondary outcomes

Unpaired t-tests will be used to compare mean knowledge scores at follow-up. Fisher’s exact test will be used to compare proportions of sufficient knowledge after counselling and at follow-up. Participants will be rated as having sufficient knowledge if they correctly answered at least 8 out of 12 questions. Unpaired t-tests will be used to compare average individual differences between planned and achieved values of blood pressure and HbA1c. Fisher’s exact tests will be used to compare the groups regarding rates of individual goal achievement (yes/no): statin choice, smoking status, blood-pressure (defined as reaching 80% to 120% of the goal), and HbA1c (defined as reaching 80% to 120% of the goal). Mann Whitney U-Test will be used to compare the medication uptake from T1 to T2 (increase/unchanged/decrease).

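### The numeracy objective is tested after the 12-question knowledge score is cut to pass/fail, which costs power unless scores are very widely spread

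*Protocol article*

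**What the plan says.** The Objectives section of the protocol article lists as an additional objective whether "patients presenting high numeracy levels achieve better knowledge than patients presenting low numeracy".

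The Sub-group analyses section sets up the test: "Two groups of participants will be defined regarding their level of knowledge (sufficient / insufficient"). The cut comes from the Secondary outcomes section: "Participants will be rated as having sufficient knowledge if they correctly answered at least 8 out of 12 questions". Fisher's exact "tests will be used to assess if knowledge is associated with the level of numeracy (yes/no) and with achievement of goals (yes/no").

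The same score is kept whole elsewhere. Under Primary outcome and Secondary outcomes, mean knowledge scores are compared by unpaired t-test, after counselling and at follow-up. Within Sub-group analyses, the paired t-test in the intervention group and the Spearman correlation ("Rho correlation coefficient will be used to assess if knowledge is associated with social status") also imply the score. No reason is given for cutting it in the numeracy analysis.

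**The concern.** The objective concerns a difference in the level of knowledge. After the cut, a patient with 0 correct answers counts the same as one with 7, and one with 8 the same as one with 12. Any numeracy difference that does not move patients across the line between 7 and 8 is lost.

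At stake is how one stated additional objective can be read. If the planned test has roughly an even chance of detecting a moderate numeracy effect, a non-significant result says little. Most of that weakness could be avoided, because the finer data are collected anyway.

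**Working it through.** **The plan's own figure.** The Sample size section assumes 70% against 50% correct, SD 0.4, two-sided 5% and 80% power. The normal approximation gives n = 2 × (1.96 + 0.8416)² × (0.4/0.2)² = 62.8, so 63 per arm. The noncentral t gives 63.8, so 64 per arm, with 80.1% power. The stated 64 per group (128 analysed) is reproduced. It applies to the comparison of arms; no power is stated for the numeracy analysis.

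**Upper bound on what the cut keeps.** For a roughly normal score, the share of information kept by a cut is φ(c)²/[p(1−p)], where p is the proportion rated sufficient.
- p = 0.5: 0.3989²/0.25 = 0.637
- p = 0.3: 0.576
- p = 0.2: 0.490

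At best, 128 patients then count as about 0.637 × 128 ≈ 82.

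**Power at the trial's size.**
- From the document: 128 analysed, arm means 0.70 and 0.50, 12 questions, cut at 8.
- Assumed: numeracy effect of 0.5 within-arm SD, half the patients with high numeracy, numeracy unrelated to arm, beta-binomial score, within-arm SD of 0.16 to 0.40.

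The t-test can be checked by hand. Ignoring arm adds variance 0.10² to the score, so the total SD is √(SD² + 0.01), and the noncentrality is (0.5 × SD/total SD) × √32.
- SD 0.16: total SD 0.189, difference 0.08/0.189 = 0.424, noncentrality 2.40, power 66%.
- SD 0.30: total SD 0.316, difference 0.15/0.316 = 0.474, noncentrality 2.68, power 76%.
- Arm term in the model, any SD: noncentrality 0.5 × √32 = 2.83, power 80%.

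Simulation (2,000 runs per cell for SD 0.16 to 0.35; Monte Carlo error about 1 point) gives:

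| Within-arm SD | Fisher on ≥ 8 of 12 | t-test on score | Score with arm term | Gap, t-test minus Fisher |
|---|---|---|---|---|
| 0.16 | 41% | 66% | 81% | 25 |
| 0.20 | 44% | 71% | 81% | 27 |
| 0.25 | 48% | 74% | 79% | 26 |
| 0.30 | 53% | 75% | 79% | 22 |
| 0.35 | 60% | 76% | 79% | 16 |
| 0.40 | about 70% | about 76% | – | about 6 |

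With 30% rather than 50% of patients in the high-numeracy group, and SDs of 0.16 to 0.35, Fisher's test has 36 to 56%, the t-test 59 to 69% and the model with arm 71 to 74%.

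**Where the loss comes from.** With the effect scaled so that the t-test has close to 80% power, Fisher's test has 51.1, 53.4, 53.9 and 56.8% at SDs of 0.16, 0.20, 0.25 and 0.30. An uncorrected chi-square test on the same cut has 55.6, 58.3, 59.6 and 62.3%. So about 5 points are due to the conservatism of Fisher's test and the rest of the gap to the cut. The gain from the t-test to the model with arm is covariate adjustment and has nothing to do with coding.

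**The case against.** The best argument against the point is the protocol's own SD. At 0.4 the cut costs only about 6 points, so a reader who takes the planning value at face value has little to complain about. This stands, and it limits the claim. It is, however, the case most favourable to a cut. On a 0-1 scale, the largest possible SD is √(0.7 × 0.3) = 0.46 at a mean of 0.7 and 0.50 at a mean of 0.5, so an SD of 0.4 requires patients clustered near both ends. At every smaller SD examined the loss is larger, and in no scenario did the cut do better.

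Second, the threshold is prespecified and already serves a secondary outcome, so it is not a data-driven split. That is true, and it supports reporting the proportions. It does not explain why the numeracy objective should be tested on them.

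Third, these are sub-group analyses with no power claim, and the comparisons between arms do not depend on them. That also stands.

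A reader might infer more than the document supports:
- **That knowledge is cut throughout.** The two-group definition is tied to the Fisher tests. The other association tests imply the score.
- **That the age analysis ("Analyses of variance (ANOVA) will be used to assess if knowledge is associated with age (groups 40–49; 50–59; 60–69")) has the same fault.** Knowledge is not cut there and age is not a listed objective. The decades cost less: 81% power falls to 62 to 66%, a relative loss of 18 to 24%. An unordered comparison can also pick up non-linear patterns, so a linear term would be a trade-off.
- **That the goal-achievement test should change too.** The Objectives section words that question as a contrast between patients with good and with poor knowledge, which gives some basis for two groups.

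**Conclusion.** The point holds for one analysis: knowledge by numeracy. The objective calls for the score, the score is available and used elsewhere, and the cut is unexplained. Under the stated assumptions the planned test has about 40 to 55% power where a t-test on the score has about 66 to 75%, for within-arm SDs of 0.16 to 0.30. The gap narrows to 16 points at SD 0.35 and about 6 points at SD 0.4.

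It would be tempting to say that a third or more of the power is lost. Relative to the t-test, that is right at SD 0.16 (25/66 = 38%) and SD 0.25 (26/74 = 35%), but not at SD 0.30 (22/75 = 29%) or at the planning SD (6/76 = 8%). The document does not give the score distribution, so no unconditional figure is justified. Nor is coding the only source of the difference: Fisher's conservatism and the omitted arm term both contribute.

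The primary result and all comparisons between arms are unaffected.

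**What to change.** In Sub-group analyses, replace Fisher's test of knowledge by numeracy with a linear regression of the 0-12 knowledge score (numeracy question excluded) on numeracy group, with a term for study arm. Report the difference in mean score with its 95% confidence interval. At minimum, use an unpaired t-test on the score, recognising that this does not bring the further gain from the arm term. Keep the sufficient/insufficient proportions by numeracy as a descriptive table. Leave the goal-achievement test and the age analysis as they are for the purpose of this point.

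The cost is a sentence of analysis wording. It needs no additional patients or data, and the named software (SPSS) can fit the model.

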### Sample size

We hypothesise patients in the ISDM group to reach higher levels of knowledge and realistic expectations. Based on pilot studies conducted during the development phase of the knowledge test, we estimate that participants having received the intervention will reach 70% correct answers in the knowledge test, whereas those having received the control-intervention will reach 50% correct answers. We calculate the sample size providing 80% power to detect an absolute difference of 20% between the intervention and the control group, using a two-tailed t-test at the 5% level of significance. Estimating a standard deviation (SD) of 0.4 in both groups, data on about 64 patients per group (128 participants) need to be included in data-analysis. Estimating a non-responder/drop-out rate of about 15%, 154 participants will need to be recruited for randomisation.

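### The planned test of knowledge against goal achievement ignores randomised arm, so it cannot tell an association with knowledge from an effect of the programme on both.

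*Protocol article*

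**What the plan says.** The Objectives section lists as an additional objective to assess "if patients with good knowledge achieve their treatment goals better than patients with poor knowledge".

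The Sub-group analyses section says how this will be answered. "Two groups of participants will be defined regarding their level of knowledge (sufficient / insufficient"), and Fisher's "exact tests will be used to assess if knowledge is associated with the level of numeracy (yes/no) and with achievement of goals (yes/no"). The cut-off is in Secondary outcomes: "Participants will be rated as having sufficient knowledge if they correctly answered at least 8 out of 12 questions".

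These sentences mention no arm. The same paragraph does limit another analysis to one arm: "T-test for paired samples will be used to assess differences in knowledge between T1 and T2 in the intervention group". The natural reading is therefore that the knowledge-by-goal table takes participants from both arms together. That is an inference from the unrestricted wording, since the article does not use the word pooled.

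**The concern.** Arm may act on both variables in this table. The Sample size section expects higher knowledge under the programme, and the key secondary objective asks whether the programme improves goal achievement. The intervention also has a route to goals that does not pass through test knowledge. Study interventions describes help with setting individual goals, and a physician is consulted if the patient wants treatment changed. The control session covers nutrition, sports and stress.

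If the programme moves both variables, the sufficient-knowledge group contains more programme patients and the insufficient group more controls. The pooled table then partly repeats the randomised contrast. A positive result could mean that better-informed patients reach their goals more often, or only that the programme raised both. A single 2x2 Fisher table has no place for an arm term, so the planned test cannot separate the two. A stated objective could be answered yes for the wrong reason.

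**Working it through.** **Inputs from the article (Sample size; Secondary outcomes).** "participants having received the intervention will reach 70% correct answers in the knowledge test"; "those having received the control-intervention will reach 50% correct answers"; "Estimating a standard deviation (SD) of 0.4 in both groups"; cut-off 8/12 = 0.667; 64 analysed per arm; two-sided 5% level.

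**The plan's own figure.** Normal approximation: n = 2 × (1.96 + 0.8416)² × (0.4/0.2)² = 62.8, so 63 per arm. The t-test version gives 63.8, so 64, with power 0.801. The stated 64 per group is reproduced. The article gives no figure for the knowledge-by-goal analysis.

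**Step 1: share with sufficient knowledge in each arm.**
- Normal score, stated SD 0.4: 1 − Φ((0.667 − 0.70)/0.4) = 0.533 under the programme; 1 − Φ((0.667 − 0.50)/0.4) = 0.338 under control.
- Normal score, assumed SD 0.2: 0.566 and 0.202.
- Binomial score, 12 items: P(X ≥ 8) = 0.724 at 70% correct and 0.194 at 50%. This implies an SD of √(0.7 × 0.3/12) = 0.13 and √(0.5 × 0.5/12) = 0.14, far below the stated 0.4, so it is an upper case.

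**Step 2: pooled association when there is none within either arm.** Let p₁, p₀ be the shares with sufficient knowledge and g₁, g₀ the goal rates. With equal arms:
- P(goal | sufficient) = (p₁g₁ + p₀g₀)/(p₁ + p₀)
- P(goal | insufficient) = ((1 − p₁)g₁ + (1 − p₀)g₀)/(2 − p₁ − p₀)

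The article gives no goal rates, so g₁ and g₀ are assumptions. For SD 0.4 and 60% vs 40%:
- sufficient: (0.533 × 0.6 + 0.338 × 0.4)/0.871 = 0.522
- insufficient: (0.467 × 0.6 + 0.662 × 0.4)/1.129 = 0.483
- odds ratio: (0.522/0.478)/(0.483/0.517) = 1.17

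**Step 3: rejection rate.** Two-by-two tables were simulated with 64 per arm and independence within arm (10,000 runs). The pooled Fisher test was compared with a Cochran-Mantel-Haenszel (CMH) test stratified by arm.

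| Goal rates (assumed) | Score model | Pooled OR | Pooled Fisher | CMH by arm |
|---|---|---|---|---|
| 50% vs 50% | SD 0.4 | 1.00 | 0.040 | 0.050 |
| 50% vs 50% | binomial | 1.00 | 0.035 | 0.051 |
| 60% vs 50% | SD 0.4 | 1.08 | 0.049 | 0.051 |
| 60% vs 50% | binomial | 1.24 | 0.080 | 0.051 |
| 60% vs 40% | SD 0.4 | 1.17 | 0.059 | 0.049 |
| 60% vs 40% | SD 0.2 | 1.36 | 0.120 | 0.052 |
| 60% vs 40% | binomial | 1.53 | 0.194 | 0.048 |
| 70% vs 40% | SD 0.4 | 1.27 | 0.093 | 0.053 |
| 70% vs 40% | SD 0.2 | 1.60 | 0.228 | 0.057 |
| 70% vs 40% | binomial | 1.92 | 0.413 | 0.047 |

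A repeat with 40,000 runs gave 0.060 and 0.189 at 60% vs 40% (SD 0.4, binomial), and 0.089 and 0.407 at 70% vs 40%.

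**Step 4: which end of the range is realistic.** A normal score with SD 0.4 puts about 27% (mean 0.70) and 21% (mean 0.50) of scores outside 0 to 100%. A bounded 12-item score with SD 0.4 gives rejection rates of 0.07 at 60% vs 40% and 0.10 at 70% vs 40%, still near the low end. The binomial case assumes that all patients within an arm have the same chance of a correct answer, so it separates the arms more than real data would.

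**The case against.** **The objective is descriptive.** The article speaks of association and of achieving goals better. A reader might infer that the trial claims knowledge drives goal achievement, but no such causal objective is stated. As a description of the whole trial population, a pooled odds ratio above 1 is a real marginal association. This stands. The rejection rates above are errors only for the within-arm question. Yet the pooled association would then depend on the trial's own mix of programme and control patients, which limits its use.

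**Knowledge may be the pathway.** The Background presents information as a way to strengthen behaviour control by removing knowledge deficits. If the programme's effect on goals runs wholly through knowledge, the pooled association is genuine. This also stands, so independence within arm is a limiting case and not the trial's model. The planned test still cannot show which case applies.

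**Arm differences in goals may be small.** Blood pressure and HbA1c goals count as reached at 80% to 120% of the goal. For illustration only, a goal of 7.5% would accept 6.0% to 9.0%, the whole HbA1c range for entry. With a ten-point difference (60% vs 50%), rejection is only 0.05 to 0.08. Statin and smoking goals have no such band.

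**The groups are not close copies of the arms.** A reader might infer that the table largely repeats the randomised comparison. At SD 0.4 the sufficient group is 0.533/0.871 = 61% programme and the insufficient group 0.662/1.129 = 59% control, which does not support that.

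**Numeracy.** A reader might extend the point to the numeracy test. Nothing in the article says that the programme changes numeracy, and randomisation balances it in expectation, so arm is not a common cause there.

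**Detail left to a fuller plan.** A journal article condenses its protocol. Here, however, it names the test, and that test cannot carry an arm term.

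**Conclusion.** The point holds as a limited one. The knowledge-by-goal test, as worded, can pick up the programme's effects on both variables and cannot separate them from an association with knowledge. With no within-arm association, the pooled odds ratio is about 1.2 to 1.5 at 60% vs 40%, with rejection in about 6% to 19% of trials. At 70% vs 40% it is about 1.3 to 1.9, with rejection in about 9% to 41%. The low ends use the article's SD of 0.4 and the high ends the binomial score, so the high ends should not be quoted alone. Stratifying by arm holds the rate at about 5% throughout.

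This rests on reading the test as covering both arms, on assumed goal rates, on 64 per arm with goal data, and on a programme effect on both knowledge and goals. If the programme leaves goal achievement unchanged, there is no inflation. Only an additional objective is at stake.

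**What to change.** Replace the single Fisher test of knowledge against goal achievement with an analysis stratified by arm. This can be a Cochran-Mantel-Haenszel or exact stratified test, or logistic regression of goal achievement at 6 months (T2) on knowledge after counselling (T1) with arm in the model. Report the estimate within each arm beside the stratified result. Using T1 knowledge ensures that it precedes the outcome. The numeracy test need not change on this ground.

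The change is one of analysis wording. It needs no new data, visits or patients, and it costs slightly lower precision for an exploratory estimate. It removes the contribution of arm only; other differences between well and poorly informed patients remain, so the result should still be reported as an association.

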An informed shared decision making (ISDM) programme on the prevention of heart attack in type 2 diabetes has been developed [16,17]. In terms of a complex intervention [18], it includes a number of interdependent components that may interact with contextual factors such as the educational background of participants and the setting. Development and evaluation of these components encompassed theoretical and empirical groundwork focusing on in-depth understanding of contextual interactions and implementation processes. Details are published elsewhere [16,17,19-21].

Key component of the ISDM-programme is an evidence-based patient decision aid (DA) [17]. The DA comprises decision relevant information on the concept of benefits and harms of different preventative options, an individual risk assessment tool, and a guide to support the decision making process. A preliminary qualitative study with diabetes educators and patients [17] indicated good acceptance and suitability to support informed decision making. Implementation of the DA is considered as optimal within patient education curricula and counselling programmes. Therefore, a patient counselling module was developed [16] related to the DA (updated 08/2012) and based on current criteria of evidence-based patient information [10]. In order to simplify implementation, duration and structure have been adapted to current patient education modules [11,12]. The counselling module was piloted within the target group and iteratively optimised [16]. In order to enable diabetes educators to successfully apply the counselling, a train-the-trainer module has been developed, consisting of a video with examples and instructions, and a structured training-session.

Since piloting of the components of the ISDM programme demonstrated feasibility and acceptance, evaluation of the efficacy of the programme in a randomised-controlled trial (RCT) is required prior to implementation [18]. In addition, concurrent qualitative research is needed to monitor and to ensure reliability and validity of the intervention [22].

The reporting of this study follows current statements [23-25].

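### The tests of knowledge against social status and age leave out study arm: they are slightly less precise than they could be and cannot show who benefits (minor).

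*Protocol article*

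**What the plan says.** The Sub-group analyses section lists association tests. For social status, Spearman's "correlation coefficient will be used to assess if knowledge is associated with social status". For age, in three ten-year bands, "Analyses of variance (ANOVA) will be used to assess if knowledge is associated with age". Neither sentence mentions study arm. The only test in the section that names an arm is a before-after comparison without a control: "T-test for paired samples will be used to assess differences in knowledge between T1 and T2 in the intervention group". The comparisons of ISDM with control, under Primary outcome and Secondary outcomes, are all for the whole sample.

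The Objectives section words the relevant aim as an association: the trial asks "if social status correlates to the level of knowledge". The Background describes the programme as a complex intervention whose components "may interact with contextual factors such as the educational background of participants and the setting". Age and social status are listed among the baseline characteristics under Data collection. Educational background is not listed as a separate variable, so social status is the nearest covariate that the plan analyses.

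**The concern.** A section called sub-group analyses is usually read as saying for whom the intervention works. Here no listed test compares the arms within a sub-group or contains an arm-by-factor term. A single correlation over both arms averages the status gradient of patients who had the programme with that of patients who did not.

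Two things follow. First, the planned difference between arms sits in the error of the association test and costs some precision. Second, the same correlation can arise when the programme helps patients of high status most, when it helps those of low status most, and when it helps all equally. A reader who takes a positive correlation as evidence on who benefits would have no basis for doing so.

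**Working it through.** **Inputs from the protocol article, Sample size.** 70% against 50% correct (a 20-point difference), SD 0.4 (40 points), two-sided 5% level, 80% power, 64 per group analysed. The plan's figure reproduces: an exact two-sample t-test with standardised effect 20/40 = 0.5 needs 63.8, so 64 per arm, with power 80.1%.

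**Assumptions, not in the document.** Three equal social-status levels coded -1, 0, 1 (variance 2/3), and a mean programme effect of 20 points. The SD is taken as 40 points (the protocol's value) and as 20 points for comparison. The status gradients, in points per level, are:

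| Scenario | Control gradient | ISDM gradient | Programme effect, low/middle/high | Average gradient |
|---|---|---|---|---|
| A | 5 | 5 | 20/20/20 | 5 |
| B | 0 | 10 | 10/20/30 | 5 |
| C | 10 | 0 | 30/20/10 | 5 |

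**Step 1: what the pooled statistic sees.** With equal arms, the pooled slope is (control gradient + ISDM gradient)/2 = 5 in all three scenarios. A simulation of the planned Spearman test (5,000 runs per scenario) agrees:

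| SD | Mean pooled rho, A/B/C | Significant, A/B/C |
|---|---|---|
| 40 points | 0.10/0.10/0.10 | 19%/18%/18% |
| 20 points | 0.18/0.17/0.17 | 52%/49%/49% |

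The planned test does not separate the scenarios at either SD.

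**Step 2: precision lost by omitting arm.** A 20-point difference between equal arms adds (20/2)² = 100 to the variance. The SE of the status slope is √(residual variance)/√(128 × 2/3), and the denominator is 9.24.
- SD 40: without arm √(1600 + 100)/9.24 = 4.46; with arm 40/9.24 = 4.33. The SE is 3% larger without arm.
- SD 20: without arm √(400 + 100)/9.24 = 2.42; with arm 20/9.24 = 2.17. The SE is 12% larger without arm. For a slope of 5, power is about 64% with arm (5/2.165 = 2.31), against about 52% for rho.

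**Step 3: what an arm-by-status term could detect.** The SE of the difference in gradients is SD × √(2/(64 × 2/3)) = SD × 0.2165. The true difference is 10 points per level in B and C.
- SD 40: SE = 8.66, ratio 10/8.66 = 1.15, power about 21%. The simulation gives 21% and 22%, and 5% under A.
- SD 20: SE = 4.33, ratio 2.31, power about 64%. The simulation gives 64% in both, and 5% under A.

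The mean estimates are close to 0, +10 and -10 points per level, so the term separates the scenarios on average. At SD 40, however, its 95% CI is ±1.96 × 8.66 = ±17 points per level. Within one status level (about 21 per arm), the CI for the programme effect is ±1.96 × 40 × √(2/21.3) = ±24 points.

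**Step 4: the other reading of the text.** If rho were computed in the ISDM arm alone, it would still lack the control gradient. At SD 20 it is positive both without interaction (A, 0.20) and with it (B, 0.38).

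**The case against.** The strongest reply is that the plan does what it says. The Objectives ask whether social status correlates with knowledge, and a rank correlation answers that. No objective, outcome or hypothesis asks whether the programme's effect differs by status or age. This stands. A reader might infer that the plan fails its own objective, and the document does not support that.

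Nor does the Background commit the trial to a moderation test. A reader might infer that the authors expect an interaction with educational background, but the text says only that one may occur. It adds that contextual interactions were studied during development, and this trial plans qualitative work on implementation processes. Educational background is also not the same as social status, and age is not named there.

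A third reply concerns power. A reader might infer that an interaction test would usually settle who benefits. The 64% in Step 3 rests on half the protocol's SD; at SD 0.4 the figure is about 22%, so such a test would usually miss even a 10-point-per-level interaction. A trial of this size may reasonably choose not to test interactions.

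What survives is narrower. The heading promises more than the tests deliver. Arm is known and planned to matter, yet it is left out of the association tests. The question raised in the Background could be described from data already collected.

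**Conclusion.** The point holds as a minor improvement. The planned tests address the association objectives, but with slightly more error than a model with arm: the SE of the status slope is about 3% larger at SD 0.4 and 12% larger at SD 0.2. They say nothing on whether the programme's effect differs by social status, since rho is the same (about 0.10 at SD 0.4, about 0.17 at SD 0.2) under opposite patterns of benefit. That the arms are pooled is inferred from the text, which restricts only the paired test to one arm; computing rho in the ISDM arm alone would not remove the problem.

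The figures rest on three assumed equal status levels, an average gradient of 5 points per level and normal scores. That the pooled slope is identical across the scenarios does not depend on the SD; the power figures do. The primary analysis, the secondary arm comparisons and the sample size are not affected.

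**What to change.** For social status and for age, fit the knowledge score on arm and the factor, and report the factor's coefficient with its 95% CI as the answer to the association question. Spearman's rho can stay as a descriptive figure, since a linear trend over status levels is an added assumption.

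Then choose one of two:
- Add the arm-by-factor term as an exploratory analysis and report the ISDM-minus-control difference with its 95% CI at each level, stating that these are estimates and not tests.
- Rename the section association analyses and state that no conclusion will be drawn on who benefits.

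The cost is a change of analysis wording; no new data, visits or patients are needed. The drawback of the first option is imprecision: with about ±24 points per status level at SD 0.4, the intervals will be wide, and a non-significant interaction must not be read as equal benefit.
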